#### Control intervention

The participants allocated to the control group will receive a minimal intervention consisting of the available fatigue-related information of the airline company. This information is normally scattered throughout the company and by putting it to the study website it is made sure that the information is available for each participant. Minimal intervention strategies are commonly used for control groups in order to compare them to an intervention group [30].

Consequently, the researchers will send an e-mail to the participants with instructions how to obtain and use the advices. The members of the intervention group will receive a link to download the smartphone application and a link to access the intervention website. The participants of the control group will be invited to log in to the study website, after which they will be directed to the standard available information. During the intervention period, all participants will be kept involved by sending a regular newsletter with information about the study in general, and upcoming questionnaires. Reminders will be sent to increase compliance among all participants, and communication throughout the airline company will be used to raise awareness.

### Outcomes

Measurements will take place at three moments; participants will be asked to fill in questionnaires at baseline (T0), and at three (T1), and six months after baseline (T2). Before each follow-up measurement, subjects from both groups will receive an e-mail in which they are asked to fill out the online questionnaires. Reminders will be sent to increase the response rate. All questionnaires are in Dutch.

#### Primary outcome

The primary outcome variable is fatigue. Fatigue will be measured using the 20-item Checklist Individual Strength (CIS) [31]. The questionnaire consists of four dimensions; the subjective experience of fatigue, reduction in motivation, reduction in activity, and reduction in concentration. It has been found that the questionnaire has a good internal consistency: the Cronbach’s α for the total CIS was 0.90 and for the scales the α ranged from 0.83 to 0.92 [31].

The questions have seven answer options, ranging from “yes that is correct” to “no that is not correct”.

#### Secondary outcomes

•*Sleep*

Sleep quantity and quality as well as timing of sleep will be measured using the Jenkins Sleep Scale [32] and the subscales subjective sleep quality, sleep latency, sleep duration, and use of sleeping medication of the Pittsburgh Sleep Quality Index [33].

The Jenkins sleep scale is a short, 4-item, multiple choice questionnaire, which is regularly used in flight personnel [34]. The internal consistency has been found to be reasonable, with a Cronbach’s α of 0.79. The used subscales from the Pittsburgh Sleep Quality Index comprise 5 multiple choice items. The total component scores of the PSQI proved to have an overall Cronbach’s α of 0.83, indicating a good internal consistency.

•*Nutrition*

Nutritional behaviour will be measured using a self-developed questionnaire. The questionnaire contains 13 questions concerning the regularity of meals taken, snacking, usage of breakfast, composition of meals, and drinking habits. The questionnaire comprises different types of questions, both open and multiple choice.

•*Physical activity*

The amount of physical activity during leisure time will be measured using questions on the recommended quantity for physical activity and exercise in healthy adults [35,36]. These measurements are often used in RCTs and comprise two open-ended questions.

•*Need for recovery*

Need for recovery will be measured using the 11-item ‘need for recovery scale’ from the Dutch Questionnaire on the Experience and Evaluation of Work (Dutch abbreviation VBBA), which has shown to be valid and reliable, and to have a good internal consistency of 0.88 [37]. All questions have two answering categories (yes / no).

•*Sickness absence*

Data on sickness absence (number of absence days and number of spells), will be collected from the records of the Occupational Health Service and Human Resource department of the airline company.

•*Work-private life balance*

Work-private life balance will be measured using the shortened version of the SWING questionnaire [38]. This 17-item questionnaire has been developed to measure and distinguish four types of interaction; negative work-home interference, positive work-home interference, negative home-work interference, and positive home-work interference. It has been shown that the questionnaire measures all constructs reliably, with Cronbach’s α’s ranging from 0.75 to 0.84 [39].

•*General Health*

General perceived health will be measured using two questions of the Dutch version of the SF-36 Health Survey which have proven to be moderately valid and reliable (0.81) [40].

•*Knowledge*

During each measurement, the knowledge of the participants regarding the relevant fatigue-related information will be measured by means of 20 true or false statements, containing all sub-domains (exposure to daylight, sleeping, physical activity, and nutrition) of the intervention.

•*Body Mass Index (BMI)*

Participants will be asked for their body height and body weight. Afterwards BMI will be computed as body weight divided by the square of height (kg/m^2^).

#### Other study parameters

•*Socio-demographic variables*

At baseline, socio-demographic data (age, gender, job title, flight unit, and household composition) will be collected.

•*Morningness-eveningness.*

At baseline, personal morningness-eveningness preference will be measured using the VOA, the Dutch version of the Morningness-Eveningness Scale (MEQ) [41].

•*Tobacco and alcohol*

Smoking tobacco and alcohol consumption are potential effect modifiers. Therefore, tobacco smoking behaviour and alcohol consumption will be assessed at baseline.

•*Chronic disease*

Having any kind of chronic disease might also be acting as an effect modifier. Therefore having a chronic disease will be measured by one yes or no question: “do you have a chronic disease?”

### Process evaluation

Besides the effect evaluation, the process of the implementation of the intervention will be evaluated, in accordance with the Steckler&Linnan framework [42]. During the intervention period, an extensive userlog will be kept, and the delivery of the intervention will be quantified. Besides, the extent to which participants use the intervention will be objectively measured through the control management system (CMS) of the application. This system will measure the number of times the intervention participants will request an advice, and, each month, all data about usage will be stored in a database. Likewise, the number and duration of all the participants’ visits to the study website will be stored as well.

Using the questionnaires, the participants will be asked if they have read and used the advices, and if they think their behaviour (regarding exposure to daylight, sleep, physical activity and nutrition) and their timing of this behaviour, has changed due to the advices. Further, they will be asked about their satisfaction with the intervention program, concerning both the smartphone application and the website.

### Statistical analysis

To investigate the success of the randomisation procedure, potential confounders or effect modifiers (age, gender, type of aircraft flown, household composition, morningness-eveningness) will be compared between the intervention and control group by Student t-tests for independent samples and Chi square tests (χ2).

The effectiveness of the intervention (time*group interaction) will be analysed using linear mixed model analyses with the outcome measures at follow-up (T1-T2) as the dependent variables. The dependent variables are fatigue, sleep, physical activity, nutrition, need for recovery, sickness absence, work-private life balance, general health and knowledge, whereas research condition (intervention or control group) is the independent variable. Possible confounding or mediating factors will be considered.

A detailed analysis plan will be developed prior to finalisation of the dataset. For all analyses a two-tailed significance level of <0.05 will be considered statistically significant. The analyses will be performed using PASW 20.0 (SPSS Inc. Chicago, Illinois, USA).

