### Randomisation

Study group allocation will be conducted at individual level, using the minimisation technique. After the baseline measurement the participants will be assigned to one of the two study groups. A minimisation procedure will make sure that the group allocation of the next participant enrolled in the trial takes into account the characteristics of those participants already enrolled. The aim is that each allocation should minimise the imbalance across multiple factors [29]. The factors that are considered for minimisation are aircraft type (five different types of aircraft units), and job title (captain, first officer, and second officer).

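### Baseline significance tests say little about a minimised allocation and nothing about effect modification; the adjustment of the primary model should be fixed in advance instead

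*Protocol article*

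**What the plan says.** The Statistical analysis section gives the baseline comparison a stated purpose and object: "To investigate the success of the randomisation procedure, potential confounders or effect modifiers". The variables are listed as "age, gender, type of aircraft flown, household composition, morningness-eveningness". They "will be compared between the intervention and control group by Student t-tests for independent samples and Chi square tests". The threshold is general: "For all analyses a two-tailed significance level of <0.05 will be considered statistically significant".

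Under Randomisation, allocation is individual and by minimisation: "The factors that are considered for minimisation are aircraft type (five different types of aircraft units), and job title". One of the five tested variables is therefore balanced by design. Job title, the other minimisation factor, is not in the tested list.

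Under Other study parameters the article adds that "Smoking tobacco and alcohol consumption are potential effect modifiers" and says the same of chronic disease. None of these three is among the five tested variables.

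For the effect analysis, the linear mixed model has the follow-up measures as dependent variables and research condition as the independent variable. On covariates there is one sentence: "Possible confounding or mediating factors will be considered". On timing: "A detailed analysis plan will be developed prior to finalisation of the dataset".

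**The concern.** Three questions are put to one set of tests: whether the randomisation worked, whether a variable confounds, and whether a variable modifies the effect. A baseline p-value is a poor tool for the first two and does not address the third.

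- **Randomisation.** If the minimisation is run as described, baseline differences arise by chance. The test then examines a null hypothesis already known to be true.
- **Confounding.** Whether an imbalance matters depends on its size and on how strongly the variable predicts fatigue. Significance measures neither.
- **Effect modification.** This is a difference in treatment effect across levels of a variable. It is seen in a group-by-modifier term, not in a comparison of arms before treatment.

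What is at stake is the primary model. The article names no adjustment variable, puts mediators beside confounders, and sets a deadline for the detailed plan that does not rule out settling these choices after outcomes can be seen by arm. Adjusting for a mediator such as knowledge or sleep behaviour could remove part of the effect the trial is meant to estimate.

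**Working it through.** The article gives no figure of its own for this point, so there is none to reproduce.

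**1. False alarms.** Inputs: five tested variables and a 0.05 level (Statistical analysis); aircraft type is a minimisation factor (Randomisation). I take the aircraft type tested to be the aircraft type minimised.

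For k independent tests under correct allocation, P(at least one p < 0.05) = 1 − 0.95^k.
- Four variables not minimised: 1 − 0.95^4 = 0.185.
- All five: 1 − 0.95^5 = 0.226. This counts aircraft type as an ordinary 5% test, which it is not, so 18.5% is the figure to use.

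Independence is an assumption. If the four tests moved together completely the figure would be 5%. Whatever the dependence, it cannot exceed 4 × 0.05 = 20%. A variable tied to rank or aircraft, as age may be, is partly balanced by the minimisation, which would lower the figure.

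**2. The test on aircraft type.** I used a simulation of minimisation on aircraft type and job title with 656 participants (Sample size) and 1,000 trials per setting. Assumptions: five equally common aircraft types; job-title shares of 45%, 45% and 10%; the preferred arm assigned with probability 1.0 or 0.8.

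| Assignment probability | Aircraft-type chi-square, p < 0.05 | Unrelated continuous variable, p < 0.05 |
|---|---|---|
| 1.0 | 0 of 1,000 | 4.5% |
| 0.8 | 0 of 1,000 | 6.1% |

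The test on the minimised factor is practically empty. The other behaves like any 5% test.

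**3. A non-significant imbalance can still matter.** Inputs: 656 / 2 = 328 per arm; SD 19.8 for the fatigue score (Sample size). The correlation ρ between covariate and outcome is not given, so I show 0.3, 0.5 and 0.7.

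- Largest standardised difference that just misses significance: 1.96 × √(2/328) = 0.153.
- Shift in the unadjusted fatigue difference: ρ × 0.153 × 19.8.
- Conditional type I error of an unadjusted comparison, given that imbalance: 1 − Φ[(1.96 − 1.96ρ)/√(1 − ρ²)] + Φ[(−1.96 − 1.96ρ)/√(1 − ρ²)].

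| ρ | Shift (points) | Conditional type I error | Residual variance after adjustment, 1 − ρ² |
|---|---|---|---|
| 0.3 | 0.9 | 7.9% | 0.91 |
| 0.5 | 1.5 | 12.9% | 0.75 |
| 0.7 | 2.1 | 20.5% | 0.51 |

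The tests would pass every one of these as balanced. The error rates are conditional on an imbalance at the edge of significance and on leaving the covariate out. They are not the error rate of the trial as a whole. The last column shows the gain from pre-specified adjustment, whether or not an imbalance occurs.

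**4. Effect modification.** A baseline comparison uses no outcome data, so it cannot carry information on whether the treatment effect differs between, say, morning and evening types.

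**The case against.** The strongest reply is that the tests may be harmless. The article attaches no action to a significant result, and the sentence on confounding and mediating factors comes later, in the mixed-model text, with no link to the tests. A reader might infer that the p-values screen confounders and leave the primary covariates data-driven. The document does not say so, and that reading is not supported. Without that link, 18.5% is the chance of a spurious flag in a baseline table, not of a biased estimate.

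Second, covariates and interaction terms may properly be left to the promised analysis plan. A reader might infer that no interaction analysis is planned for smoking, alcohol or chronic disease. A condensed article that defers detail does not support that inference, and collecting these variables as possible modifiers is compatible with a later interaction analysis.

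Third, a gross imbalance can reveal a broken allocation, so a baseline check has some use. That is true, but descriptive counts and means would show it without a p-value.

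Fourth, it is tempting to call this an open trial whose analysts see results by arm. The Strengths & limitations section says only that participants are not blinded; nothing is said of analysts.

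What remains after these replies is stated text: the tests, their purpose, the label of effect modifiers on the tested variables, the open covariate sentence with mediators in it, and the deadline for the plan.

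**Conclusion.** The point holds as one of method and timing. The stated tests are a weak check on a minimised allocation: about 18.5% chance of at least one false imbalance over the four non-minimised variables if independent, and an almost certain non-significant result for aircraft type. They do not show whether an imbalance matters, and they are silent on effect modification.

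The consequence for the primary result is indirect. It comes from a model that names research condition and no covariate, from mediators being open for consideration, and from a plan due only before the dataset is final. The shifts of 0.9 to 2.1 points and conditional error rates of about 8% to 21% illustrate why significance is the wrong yardstick; they rest on assumed correlations and an unadjusted analysis, neither of which the article states. This is an improvement worth making at almost no cost, not evidence that the planned result would be biased.

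**What to change.** In the Statistical analysis section:

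1. Replace the t-tests and chi-square tests with a descriptive table of baseline characteristics by arm, and include job title, smoking, alcohol and chronic disease.
2. Pre-specify that the primary model adjusts for the T0 value of the outcome, aircraft type and job title, whatever the observed balance.
3. State that the primary effect is not adjusted for mediators; any mediation analysis is separate and secondary.
4. Examine any effect modifiers through group-by-modifier terms, with the modifiers listed in advance and the results labelled exploratory.
5. Change the deadline so that the analysis plan is complete before any follow-up outcomes are viewed by group.

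The T0 outcome, flight unit, job title and the named modifiers are already collected at baseline. The cost is wording and earlier drafting of the plan; no added data, participants or staff are needed.

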### Sample size

The sample size is based on finding an effect on the primary outcome of the intervention, perceived fatigue. Fatigue will be measured using the 20-item CIS questionnaire [43]. The mean total score on this questionnaire for healthy employees is 47.3 (SD = 19.8) according to Beurskens et al. [43] (score range 0–140). Power calculations indicate that to detect a relevant 10% difference in fatigue, 246 subjects are necessary in each study group (with power = 0.80 and alpha = 0.05). Taking the expected loss to follow-up (25%) into account, a sample size of approximately 656 employees is required.

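### The baseline (T0) score has no stated role in the outcome model, so the time*group term tests only change between 3 and 6 months, and the group effect loses precision

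*Protocol article*

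**What the plan says.** The Outcomes section says "participants will be asked to fill in questionnaires at baseline (T0"), and again at three months (T1) and six months (T2). Under Study procedures and Randomisation, allocation follows receipt of the completed baseline questionnaire, so every randomised pilot has a pre-allocation CIS score.

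The Statistical analysis section equates effectiveness with a time*group interaction in a linear mixed model. It takes the T1–T2 follow-up measures as the dependent variables, "whereas research condition (intervention or control group) is the independent variable". It adds, without naming any, that confounders or mediators may be taken into account, and it promises a fuller analysis plan before the dataset is finalised. Baseline CIS is also not among the variables to be compared between groups as a check on randomisation. Minimisation uses aircraft type and job title only.

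The Sample size section gives the inputs for the primary outcome: "The mean total score on this questionnaire for healthy employees is 47.3 (SD = 19.8"), a target "to detect a relevant 10% difference in fatigue", and "246 subjects are necessary in each study group (with power = 0.80 and alpha = 0.05").

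**The concern.** The section does more than leave covariates for later. It fixes the set of responses and names the predictor, and T0 is in neither. That has two consequences for the primary outcome.

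First, the effect named as the measure of effectiveness may not answer the trial's question. If the only time levels are T1 and T2, the interaction compares the group difference at six months with the group difference at three months. An intervention that lowered fatigue by the same amount at both visits would show no interaction.

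Second, part of the between-person variation in CIS at follow-up can be predicted from the same person's T0 score. Without T0 in the model, that variation stays in the error term, and a chance difference between the groups in baseline fatigue carries partly into the estimate. Minimisation does not balance baseline fatigue.

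**Working it through.** **Inputs.** Mean 47.3, SD 19.8, 10% difference, 80% power, alpha 0.05, 246 per group and 25% loss are from Sample size. Two-sided testing is from Statistical analysis ("For all analyses a two-tailed significance level of <0.05 will be considered statistically significant"). The correlations are assumptions, because the article gives none.

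**1. The plan's own figure.** n per group = 2 × [SD × (1.960 + 0.842) / Δ]².
- Δ = 10% of 47.3 = 4.73: 2 × (19.8 × 2.802 / 4.73)² = 275.1, so 276 per group. This does not reproduce 246.
- Δ = 5.0: 2 × (19.8 × 2.802 / 5)² ≈ 246.2. This matches 246.
- Loss to follow-up: 2 × 246 / 0.75 = 656, as stated.

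**2. What the interaction tests.** With T1 and T2 as the only time levels, the contrast is (difference at T2) − (difference at T1). For a constant benefit of 4.73 points it is (−4.73) − (−4.73) = 0.

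**3. Single follow-up, with and without T0.** Residual SD = 19.8 × √(1 − r²). Standard error = residual SD × √(2/246). Power ≈ Φ(4.73 / standard error − 1.96).

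| assumed r | residual SD | power at 246 per group | n per group for 80% |
|---|---|---|---|
| 0 (unadjusted) | 19.80 | 75.5% | 276 |
| 0.3 | 18.89 | 79.3% | 251 |
| 0.4 | 18.15 | 82.4% | 232 |
| 0.5 | 17.15 | 86.4% | 207 |
| 0.6 | 15.84 | 91.2% | 177 |
| 0.7 | 14.14 | 96.0% | 141 |

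Break-even for 80% at 246 per group: r = √(1 − 246/275.1) ≈ 0.33.

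If the target was 5.0 points, unadjusted power is 80.0%, and adjustment gives 83.5% at r = 0.3, 89.9% at r = 0.5 and 97.5% at r = 0.7.

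**4. Average of T1 and T2.** Assume that all correlations among T0, T1 and T2 are 0.5. Variance relative to a single measurement:
- Unadjusted: (1 + 0.5)/2 = 0.75, SD 19.8 × √0.75 = 17.15, power 86.4%.
- Adjusted for T0: 0.75 − 0.5² = 0.50, SD 19.8 × √0.50 = 14.00, power 96.3%.

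Adjustment removes a further third of the variance.

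**5. Chance imbalance.** Taking SD 19.8 at baseline as well, the standard error of the T0 difference with 246 per group is 19.8 × √(2/246) = 1.8 points, so 95% of allocations fall within about ±3.5. Unadjusted, r times that difference carries into the estimate. At r = 0.5 this is up to about 1.75 points, or 1.75/4.73 = 37% of the target.

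**The case against.** The strongest reply is that this is a condensed article. It leaves room for covariates and promises a detailed plan, and the choice of covariates normally belongs there. This stands in part: a reader might infer that the plan rules out baseline adjustment or uses group alone as predictor, and the text supports neither. Time is implied by the interaction, and T0 is unnamed rather than excluded. What remains is that the section already fixes the responses as T1–T2, and on that wording the interaction does not measure the intervention's effect.

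The interaction could also mean that T0 is intended as a time level, in which case baseline is already used. That reading conflicts with the restriction of the dependent variables to follow-up. Either way, the role of T0 and the primary contrast need stating.

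Three stronger readings are tempting but not supported:

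- **That adjustment would repair a power shortfall.** This needs r above about 0.33, and no r is given. The shortfall itself disappears if the 10% was rounded to 5 points.
- **That the planned analysis has 75% power.** That figure is for a two-group comparison at one follow-up. For the T1–T2 average, unadjusted power is about 86% at an assumed T1–T2 correlation of 0.5. It stays at or above 80% while (1 + correlation)/2 ≤ 246/275.1, that is, up to a correlation of about 0.79. For the interaction, neither figure applies.
- **That a chance baseline difference biases the result.** It carries over only in proportion to r, and under random allocation the unadjusted estimator remains unbiased. Nor does absence of baseline CIS from the randomisation check show that it is excluded from the model; that list serves a different purpose.

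**Conclusion.** The point holds as one of specification and precision. As written, T0 has no role, and the named effect, taken on T1–T2 alone, does not test whether fatigue is lower in the intervention group. Adding T0 as a covariate is a definite improvement on the stated model, but its size is conditional. On the single-follow-up calculation it is worth about 4 percentage points of power at r = 0.3, 11 at r = 0.5 and 20 at r = 0.7. For the T1–T2 average it is worth about 10 points with all correlations at 0.5. These figures assume 4.73 points, SD 19.8 in pilots as in the cited healthy employees, and 246 analysed per group. The change should be made; the case for it does not depend on whether there is a power shortfall.

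**What to change.** State in the Statistical analysis section, or in the promised analysis plan before follow-up data are examined: 'Each questionnaire outcome at T1 and T2 is modelled on group, time, group-by-time and the T0 value of that outcome as a fixed covariate. The primary contrast is the adjusted group difference in CIS [at T2 / averaged over T1 and T2].' One of the two options must be chosen. The group-by-time term stays, as a secondary question about whether the effect changes between three and six months.

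Apply the same to sickness absence only if records from before baseline are available; the Secondary outcomes section gives no such collection period.

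For the questionnaire outcomes the cost is wording alone. The T0 scores are collected from every participant before allocation, so no extra participants or measurements are needed.
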